### Rescue therapy and concomitant medications

2.7

If severe unbearable pain is observed at the time of visit for screening, limited anti-inflammatory analgesics and muscle relaxants, excluding opioid analgesics and anesthetics, are permitted at the discretion of the clinical investigator providing the NBT (Medications for the digestive system are also allowed to reduce the side effects of rescue medications.). If rescue medications are used, the date and dosage of administration must be recorded in the patient journal.

The types of available rescue medications include skeletal muscle relaxants, anti-convulsant, anti-inflammatory drugs, analgesics, neuralgia drugs, anti-depressants, nonopioid analgesics, antipyretics, weak opioids, and digestive medications.

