#### Exploratory effectiveness evaluation

2.8.3

1.Additional NBT or surgery for lumbosacral radiculopathy: All patients will be assessed if they underwent any additional NBT or surgical treatment related to lumbosacral radiculopathy on the last day of visit and at 4 weeks after the end of treatment. This assessment will be not conducted on those whose symptoms have improved and ended the study earlier. For patients who dropped out in the middle of the study, the assessment will be performed at 4 weeks after dropout. However, exploratory effectiveness evaluation for dropout participants can be conducted through telephone counseling instead of in-person visits.2.Early termination of treatment: Patients whose symptoms have improved during the study, who request to terminate treatment early, and who no longer require treatment at the discretion of the investigators will be separately evaluated for each group.3.Rescue medication usage: The number of uses, dosage, type, and administration point of rescue medications used between the clinical trial period and final evaluation period will be compared between the 2 groups.

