##### Dropout criteria

2.8.7.1

1.If the patient is under prescription of the following medications that are expected to affect the safety and effectiveness of NBT and acupotomy, the medications cannot be taken from the time of screening until the completion of the study.① Concurrent use of medications that are prohibited for use with medications used for NBT.Medications that are likely to cause serious side effects in drug interaction studies.Medications whose mutual use is restricted with disodium dexamethasone injection: asunaprevir, daclatasvir, dronedarone hydrochloride, eliglustat, grazoprevir, ibrutinib, nilotinib hydrochloride monohydrate, olaparib, osimertinib, palbociclib, rilpivirine, rivaroxaban, ticagrelor, ceritinib, ribociclib, venetoclax, elbasvir, BCG strain, cobimetinib, cicletanine, etc. (Other medications used for NBT do not cause side effects of serious grade in drug interaction studies)② Strong opioid, local anesthetic administered by another physician than the one for this clinical studyHowever, anti-inflammatory analgesics and muscle relaxants prescribed for necessary causes at the discretion of the clinician can be administered^[13]^ (See rescue medications).③ Medications that may pose a risk to the patient or cause bias in the results as judged by the clinical investigator2.The patient requests to discontinue interventions or withdraws consent for participation3.The patient is judged to be unfit to continue in the study due to serious adverse reactions/medication reactions4.Serious protocol violations such as inclusion/exclusion criteria are newly discovered during the study5.Patients in the NBT and acupotomy combination treatment group who do not meet the criteria for early termination but have not conducted 6 or more of the 8 planned acupotomy treatments6.Patients who do not meet the criteria for early termination but fail to conduct even one of the planned NBT7.Patients who are judged to be unfit to continue in the study for other reasons at the discretion of the clinical investigator

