**Rate of early termination = (patients who completed the study early/patients who completed the entire study)∗100**

Analysis of rescue medication use

Independent t-test or Wilcoxon's signed rank test will be conducted to compare the number and dose of use according to different types of rescue medication between the groups.

D. Classification and post hoc analysis of responders and nonresponders

Definition of responders

(1)Those with a minimal CID decrease of NRS 2.5 from the baseline to the date of evaluation. Therefore, responders will be defined as follows. For example, pain reduction of greater than NRS 2.5 will be defined as CID, and CID will be used to divide patients into responders and nonresponders.(2)Using the previously described criteria, patients who had improved symptoms and completed the study early will be considered as responders.

Post hoc analysis

Adequate post-hoc analysis will be conducted by a statistician for differences in treatment results for each treatment group using the responder and non-responder criteria.

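### Section 2.7 contradicts itself on permitted rescue medication: opioid analgesics are excluded in one paragraph and weak opioids listed in the next, and the dropout criteria do not settle it

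*Protocol article*

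**What the plan says.** Rescue medication is dealt with in four places in the protocol article.

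- **Section 2.7, first paragraph.** The trigger is "If severe unbearable pain is observed at the time of visit for screening". In that case "limited anti-inflammatory analgesics and muscle relaxants, excluding opioid analgesics and anesthetics, are permitted at the discretion of the clinical investigator providing the NBT". Digestive drugs are added to offset side effects. The opioid exclusion is not limited to strong opioids.
- **Section 2.7, second paragraph.** This gives the types of available rescue medication. It begins with muscle relaxants, anticonvulsants and anti-inflammatory drugs and continues with "analgesics, neuralgia drugs, anti-depressants, nonopioid analgesics, antipyretics, weak opioids, and digestive medications". No period of use is given.
- **Section 2.8.7.1 (dropout criteria).** For drugs expected to affect safety or effectiveness, "the medications cannot be taken from the time of screening until the completion of the study". The opioid item names strong opioids only. The exception is that "anti-inflammatory analgesics and muscle relaxants prescribed for necessary causes at the discretion of the clinician can be administered", with a pointer to the rescue medications.
- **Sections 2.8.3 and 2.9.** As an exploratory outcome, the number, dosage, type and timing of "rescue medications used between the clinical trial period and final evaluation period will be compared between the 2 groups". The analysis will "compare the number and dose of use according to different types of rescue medication between the groups".

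Exclusion criterion 3 (section 2.5.2) is also relevant. It excludes patients on drug treatment for pain control and gives strong opioid therapy as its example.

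**The concern.** An investigator deciding whether a patient may have a weak opioid as rescue gets opposite answers from two adjacent paragraphs. For anticonvulsants, neuralgia drugs and antidepressants, the first paragraph describes a limited permission that does not include them, while the second lists them as available.

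This matters statistically for two reasons. First, rescue is left to the investigator providing the nerve block, and section 2.6 says that investigator and participant cannot be blinded to treatment. The ODI (primary) and the NRS (secondary) are reported by patients who know their arm. If the conflicting text is read differently for different patients, co-medication can come to differ between arms for reasons unrelated to the randomised treatment. Second, rescue use by type is itself compared between arms. If the plan does not settle which drugs are rescue, the same prescription may be counted as rescue for one patient and as ordinary concomitant medication for another.

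**Working it through.** The document gives no figure for rescue use, so there is none to reproduce. The check is a comparison of the texts.

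**Step 1: classes.** The second paragraph of 2.7 has ten labels. Set against the other two texts:

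| Class | 2.7, first paragraph | 2.7, second paragraph | 2.8.7.1 |
|---|---|---|---|
| Anti-inflammatory drugs | permitted | listed | permitted by exception |
| Muscle relaxants | permitted | listed | permitted by exception |
| Digestive drugs | permitted | listed | not named |
| Analgesics, nonopioid analgesics, antipyretics | anti-inflammatory analgesics only | listed | anti-inflammatory analgesics only |
| Weak opioids | excluded with all opioid analgesics | listed | not named |
| Anticonvulsants, neuralgia drugs, antidepressants | not named | listed | not named |
| Strong opioids | excluded | not listed | barred |

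Of the ten labels, 3 match the first paragraph, 3 overlap heavily with what it names, and 4 do not agree with it (3 + 3 + 4 = 10). Of those four, weak opioids are a direct contradiction. The other three are a mismatch between a limited permission and a wider list. A bare contrast of three classes with ten would overstate the gap because of the overlapping labels.

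**Step 2: does the dropout section decide between the paragraphs?** It does not. It names the narrow classes, as the first paragraph does. It bars only strong opioids, which fits the second. It then refers the reader back to the section that holds both.

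**Step 3: can the wording be read consistently?** Two readings would work: that opioid in the first paragraph means strong opioid, or that the first paragraph governs the screening visit and the second governs later visits. The document states neither. It does write strong opioid in sections 2.5.2 and 2.8.7.1, so the distinction was available and was not used in the first paragraph of 2.7.

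**Step 4: timing.** The only trigger in 2.7 is severe pain at the screening visit. Section 2.8.3 compares use up to the final evaluation. Section 2.8.7.1 places its exception inside a rule running from screening to completion, and Table 1 reviews medication at every visit after baseline. Use during the trial is clearly expected, so this is an unclear trigger more than a second contradiction.

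**Step 5: where it reaches the analysis.** The direct route is the rescue comparison in 2.8.3 and 2.9. The indirect route is co-medication acting on ODI and NRS. The per-protocol definition in 2.9 has no medication condition of its own.

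**The case against.** The strongest reply is that only the opioid wording is plainly in conflict and that little follows from it. Much of this stands.

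- **Status of the patient.** A reader might infer that a patient given a weak opioid is compliant under one rule and a violator or dropout under another. The document does not support that. No section makes such use a violation, the dropout item names strong opioids only, and the per-protocol conditions do not mention medication. The open clause in 2.8.7.1 on drugs that an investigator judges risky or biasing is a general one, and it would exist whatever 2.7 said.
- **Loss of the primary outcome.** A reader might also infer that such patients lose their week-4 ODI. That needs a dropout that no section mandates, and Table 1 schedules an ODI at dropout, although not necessarily at week 4.
- **Cost analysis.** Section 2.8.6 costs rescue and concomitant medication together, and section 2.8.5 requires all concomitant medication to be recorded in detail. The label therefore does not decide whether a drug is costed.
- **Dilution.** Allowing any rescue in a pragmatic comparison may dilute a difference, and a consistent wide list would do so too. What the contradiction adds is narrower: the permission can vary with who reads the text, and the person reading it knows the arm.
- **Comparison by type.** Analysis by drug type would show weak opioids separately. That helps only if they are consistently recorded as rescue.

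The reply does not remove the conflict. Two stated rules disagree within one section, and the cross-reference does not resolve them. This is not detail that a condensed article has left to a fuller document.

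**Conclusion.** The point holds as an internal contradiction in section 2.7. It is direct for weak opioids and a mismatch of scope for anticonvulsants, neuralgia drugs and antidepressants, and section 2.8.7.1 leaves it unsettled. The unclear period of use is a lesser point that sections 2.8.3 and 2.8.7.1 largely answer by implication.

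The consequence is room for co-medication to differ by arm in an open-label trial with patient-reported outcomes, and for an inconsistent definition of an outcome compared between arms. Neither the size nor the direction of any effect on the ODI comparison can be derived. The document gives no expected rescue rate, and a count of affected patients would rest wholly on an assumed one. The conclusion assumes only that the two paragraphs of 2.7 are both in force, as the text presents them.

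**What to change.** Reconcile section 2.7, section 2.8.3 and section 2.8.7.1 into one list of permitted and prohibited classes and one stated period of use. Check exclusion criterion 3 in section 2.5.2 against that list. Then use the same list to define rescue medication in the between-arm comparison in sections 2.8.3 and 2.9, so that every prescription is classified the same way in both arms.

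Which classes and which period apply, and whether rescue use has any bearing on dropout, are for the investigators to decide. The cost is protocol wording and a memo to the site, with no added procedures or visits.

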### Study outcomes

2.8

#### Primary outcome

2.8.1

Functional assessment will be conducted using the Korean Version of Oswestry Disability Index (ODI)^[16]^ at 0 (screening test), 2, 4, and 8 weeks compared with that before study participation will be investigated. However, considering the cultural characteristics of Korea, item number eight on sex life will not be asked.

#### Secondary outcome

2.8.2

1.NRSThe patient selects a number that corresponds to the pain level^[17]^ (NRS-11 that evaluates pain from a score of 0–10 will be used). In this study, changes in pain level will be assessed at 0 (screening test), 2, 4, and 8 weeks and compared with that before study participation. Low back pain and lower extremity pain will be separately evaluated.2.European Quality of Life 5 Dimension (EQ-5D)Changes in quality of life will be assessed at 0 (screening test), 2, 4, and 8 weeks and compared with that before study participation. EQ-5D evaluates 5 domains: mobility, self-care, usual activity, pain/disability, and anxiety/depression. It is widely used to assess quality of life.^[18]^
3.McGill Pain Questionnaire (MPQ)The Korean version of MPQ^[19]^ will be used to assess changes in pain at 0 (screening test), 2, 4, and 8 weeks and compared with that before study participation.4.Korean version of Roland–Morris Disability Questionnaire (RMDQ)The Korean version of RMDQ^[20]^ will be used to assess changes in pain at 0 (screening test), 2, 4, and 8 weeks compared with that before study participation.

#### Exploratory effectiveness evaluation

2.8.3

1.Additional NBT or surgery for lumbosacral radiculopathy: All patients will be assessed if they underwent any additional NBT or surgical treatment related to lumbosacral radiculopathy on the last day of visit and at 4 weeks after the end of treatment. This assessment will be not conducted on those whose symptoms have improved and ended the study earlier. For patients who dropped out in the middle of the study, the assessment will be performed at 4 weeks after dropout. However, exploratory effectiveness evaluation for dropout participants can be conducted through telephone counseling instead of in-person visits.2.Early termination of treatment: Patients whose symptoms have improved during the study, who request to terminate treatment early, and who no longer require treatment at the discretion of the investigators will be separately evaluated for each group.3.Rescue medication usage: The number of uses, dosage, type, and administration point of rescue medications used between the clinical trial period and final evaluation period will be compared between the 2 groups.

#### Evaluation of responders and nonresponders

2.8.4

1.Patients will be divided into groups of responders and nonresponders based on the NRS with a minimal clinically important difference (CID) of 2.5 for chronic low back pain.^[21]^ If the NRS score decreases by 2.5 or more compared with that at screening, the patient will be considered as a responder, and vice-versa.2.Patients who terminated their treatment earlier after improvement of symptoms will be included in the responder group.

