# Exploratory evaluation is not conduced for patients who have completed treatment early. For patients who dropped out of the study, exploratory evaluation is conducted after 4 weeks from dropping out (exploratory effectiveness evaluation for dropout participants can be conducted through telephone counseling instead of in-person visits).

∗∗ Evaluation of direct non-healthcare, direct non-healthcare, and lost productivity costs.

†† Those patients who reported adverse reactions will complete EQ-5D by recalling time of adverse events.

Patients who undergo 1 NBT and show continued symptoms (patient's subjective pain improvement is less than 50% after the procedure or the numeric rating scale (NRS) score being 5 or higher) will undergo screening at 1 week after the first procedure. For screening, demographic information, medical history, physical examination, vital signs, questionnaire survey, laboratory test, and selection/exclusion criteria will be evaluated. Randomization and group allocation will be performed at screening and baseline. Fifty patients will be enrolled and randomly divided into 2 groups. Patients who are judged suitable for the study after the screening test and voluntarily agree to participate will be randomly assigned to either the NBT single treatment group (usual care group) or NBT + deeply inserted acupotomy treatment group in a 1:1 ratio (Fig. 1). Thereafter, the randomly assigned patients will undergo primary and secondary outcome evaluations and economic evaluation.

The NBT + deeply inserted acupotomy group will receive 8 acupotomy treatments (at visits 2, 3, 5, 6, 7, 8, 10, and 11) for 4 weeks as well as additional 2 NBTs (at visits 4 and 9) for 4 weeks. Then, the group will be followed-up for 4 weeks after the intervention treatment. The standard care group will undergo two NBTs (at visits 2 and 4) for 4 weeks and will be followed-up for 4 weeks after the intervention treatment. Primary and secondary outcomes, economic evaluation, and assessment of drug administration history will be conducted at visits 1, 6, and 11, and at the end of follow-up. To evaluate safety, evaluation of adverse events, vital signs, and economic feasibility will be conducted at every visit from visit 2 to visit 12. Laboratory tests will be conducted only at screening.

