### Recruitment, randomization, blinding, and nonblinding

2.6

Advertisements for patient recruitment will be posted on the Catholic Kwandong University, International St. Mary's Hospital's bulletin boards, along with posters, banner advertisements, and internet cafes. All advertisements will be run after institutional review board (IRB) approval.

Individuals who provide written consent to participate in the study will be assigned a screening number, according to the order of the outpatient visit at screening. Unblinded sub-investigators, who do not influence the research results and analysis, will refer to the randomization list that has been prepared by a commissioned professional statistician, and assign participation numbers. Participants will be allocated to the NBT group and the acupotomy + NBT group in a ratio of 1: 1. A block randomization table will be generated by an independent statistician and patients will be assigned to one of 2 groups according to the randomization table. Screening numbers, randomization numbers, and initials assigned to each participant will be used as subject identification codes to identify the participant until the end of the clinical trial.

The NBT used in this study is not a clinical investigational product and does not require allocation concealment, since it is administered to all groups. Moreover, it is impossible to blind the investigator and the participant in each group due to the nature of the study intervention, which is based on the contact between the patient and the medical staff. Instead, the investigator maintains blinding to prevent bias in evaluating the participant. After the clinical trial is completed, all clinical report forms (CRFs) will be collected, the database process terminated, and unblinding performed, if required for statistical analysis. Moreover, if it is deemed necessary to confirm the subject group due to an emergency situation during the clinical trial, the randomization code will be disclosed only to the participant, according to the principal investigator's discretion. If it is not possible to consult with the principal investigator and the situation is urgent, the randomization code of the subject will be disclosed after consultation with the randomization code officer. If unblinding is performed, the documentation of the reason for the unblinding will be retained, and the participant with the disclosed randomization code will not be able to continue the trial.

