##### Criteria for early termination

2.8.7.2

1.Patients whose symptoms have improved during the study, who request to terminate early, and who no longer require treatment at the discretion of the investigators can terminate the study earlier than planned.2.Patients who have terminated the study early are not classified as withdrawn/discontinued patients and are considered to have complied with the study treatment.

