**Efficacy evaluation**
In the efficacy evaluation, ITT will be treated as the main analysis group, and PP sets will be treated as the secondary analysis group. All statistical analysis will be conducted as two-sided tests with a significance level of 5%. Two-sided 95% confidence interval will be presented. Descriptive statistics will be presented for each treatment group and visit. Descriptive statistics and 95% confidence intervals will be presented for differences between the baseline and each visit.

Among efficacy evaluation variables, missing values of continuous variables will be analyzed using baseline observation carried forward correction.

A. Analysis of primary endpoints

For symptoms of lumbosacral radiculopathy at each measurement time point, descriptive statistics (number of patients, mean, and standard deviation) of the ODI score and changes in ODI at the end of treatment (4 weeks) and follow-up (8 weeks) compared with the baseline will be presented.

Paired *t*-test or Wilcoxon's signed ranked test will be conducted for intra-group changes in ODI at the end of treatment (week 4) compared with the baseline (0) depending on the satisfaction of normality. An analysis of variance model that includes changes in ODI at the end of treatment compared with the baseline as effects and baseline ODI as covariates will be used to evaluate the effects in the treatment group compared with the control group. Differences in least-square mean between treatment and control groups will be calculated, and two-sided 95% confidence interval and *P* value for the differences will be presented.

B. Analysis of secondary endpoint

Changes in ODI at follow-up (8 weeks) compared with baselineAssessment of subjective pain intensity in patients with lumbosacral radiculopathy-Lumbosacral radiculopathy pain will be divided into lower back and lower extremity pain using NRS, MPQ, and K-RMDQAssessment of quality of life related to lumbosacral radiculopathy-Evaluation of overall quality of life using EQ-5D. The same analysis methods for primary endpoints will be used to analyze secondary endpoints

C. Exploratory efficacy evaluation

Evaluation related to additional NBT or surgery after completion of the study

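### Patients who stop early after improvement count as responders whatever their NRS, so the post hoc responder comparison can be biased towards the combination arm

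*Protocol article*

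**What the plan says.** Section 2.8.4 of the protocol article gives two separate routes to responder status. The first is measured: "If the NRS score decreases by 2.5 or more compared with that at screening, the patient will be considered as a responder". The second is by status alone: "Patients who terminated their treatment earlier after improvement of symptoms will be included in the responder group". The statistical section (2.9, part D) repeats the second route: "patients who had improved symptoms and completed the study early will be considered as responders". It is therefore a deliberate rule and not a slip in one place.

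Section 2.8.7.2 sets the condition for early termination. Symptoms must have improved, and it applies to patients "who request to terminate early, and who no longer require treatment at the discretion of the investigators can terminate the study earlier than planned". No NRS or ODI value is attached. Section 2.6 says that "it is impossible to blind the investigator and the participant in each group due to the nature of the study intervention", and goes on to say that blinding is kept for evaluation.

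On contacts, section 2.2 says the combination group "will receive 8 acupotomy treatments (at visits 2, 3, 5, 6, 7, 8, 10, and 11) for 4 weeks", with NBT at visits 4 and 9. Table 1 shows treatment-period visits 2 to 11 for that arm and visits 2 to 5 for the NBT arm. Table 1 also has an early-termination column in which the secondary endpoints, NRS among them, are ticked.

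For the continuous efficacy variables, section 2.9 states that "missing values of continuous variables will be analyzed using baseline observation carried forward correction".

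**The concern.** A responder rate is meant to summarise a measured change in pain. Under the second route, part of it records a decision to stop. That decision is made by people who know the allocation, has no threshold, and can be taken at more scheduled contacts in one arm than in the other. If some patients stopped as improved have an NRS fall below 2.5, they become successes by status. More of them may arise in the combination arm even if the treatments are equivalent.

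There is also a consistency problem. A patient who stops early and has no week-4 NRS is a responder in this analysis, but is set to no change from baseline in the continuous NRS and ODI analyses. The responder result and the mean-change results could then point in different directions for reasons unrelated to pain.

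**Working it through.** **The plan's own figure.** The only design figure is the sample size: 20 / (1 − 0.20) = 25 per arm, 50 in total, which reproduces. The protocol states no responder rate and no early-termination rate, so everything below rests on assumed values.

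**Inputs from the protocol.** Treatment-period visits are 10 (visits 2–11, combination) and 4 (visits 2–5, NBT), from Table 1. The responder threshold is 2.5 NRS points.

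**Assumed inputs.**
- q is the chance per visit of being stopped as improved, the same in both arms.
- True NRS response is 35% in both arms, so there is no treatment difference.
- r is the share of early stoppers who would meet the NRS criterion anyway.

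**Formulas.** The early-termination proportion is ET = 1 − (1 − q)^k, with k = 10 or 4. The counted responder rate is 0.35 + ET × (1 − r). The spurious gap is therefore (ET combination − ET NBT) × (1 − r).

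**Worked case, q = 2%.**
- ET combination = 1 − 0.98^10 = 18.3%; ET NBT = 1 − 0.98^4 = 7.8%; difference 10.5 points.
- If stopping is unrelated to response, r = 0.35. The counted rates are 46.9% and 40.0%, a gap of 6.8 points.
- If r = 0.8, the gap is 10.5 × 0.2 = 2.1 points. If r = 0.9, it is 1.1 points. If r = 1, it is zero.

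**Range (gap in percentage points).**

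| q per visit | ET combination | ET NBT | r = 0.35 | r = 0.8 | r = 0.9 | r = 1 |
|---|---|---|---|---|---|---|
| 1% | 9.6% | 3.9% | 3.7 | 1.1 | 0.6 | 0 |
| 2% | 18.3% | 7.8% | 6.8 | 2.1 | 1.1 | 0 |
| 3% | 26.3% | 11.5% | 9.6 | 3.0 | 1.5 | 0 |

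For scale, one patient in an arm of 25 is 4 points.

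**Check on the visit count.** Stopping at the last treatment-period visit is hardly early, so 9 against 3 visits is a fair alternative. Here q is the chance per visit that a patient below the threshold is stopped, and the counted rate is p + (1 − p)(1 − (1 − q)^k). With p = 40% in both arms:
- q = 1%: 45.2% against 41.8%, a gap of 3.4 points.
- q = 2%: 50.0% against 43.5%, a gap of 6.4 points (from unrounded rates).
- q = 5%: 62.2% against 48.6%, a gap of 13.6 points.

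If Fisher's exact test compared the proportions at 25 per arm (two-sided 5%), its false-positive rate would be 3.0% at q = 0, 5.1% at q = 2% and 12.0% at q = 5%. Over p = 30% to 50% and q = 1% to 5%, the gap runs from 2.8 to 15.9 points. Using 10 against 4 visits changes little (2.8 to 15.1).

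**What would remove the visit effect.** If requests to stop arise per week and not per visit, both arms have the same four-week treatment period. ET is then equal and the visit mechanism contributes nothing.

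**The case against.** A reader might infer that the responder rates are biased, and by about 7 points. The documents do not support that, for three reasons.

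- Early termination requires improved symptoms, a patient request and no further need for treatment. Patients who satisfy all three may well have an NRS fall of 2.5 or more, and then the second route changes nothing. The 7-point figure assumes that stopping is unrelated to response, which sits badly with that criterion.
- The protocol does not tie the decision to scheduled visits. Visits are the natural occasion, but this is an inference.
- No value of q can be taken from the text.

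These objections stand. They limit the claim to a possible bias of unknown size.

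It is also fair to say that the second route has a purpose. With baseline carried forward, an improved patient who stops and has no later NRS would otherwise be scored as a non-responder. That explains the rule but does not require it, because an NRS is already scheduled at the early-termination visit.

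The NRS is not discarded altogether, since it remains a continuous secondary endpoint; only the responder classification overrides it. Early termination is already compared between arms as a separate exploratory outcome (2.8.3 and 2.9, part C), so a reader of the results could see how many responders might come from this route.

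Finally, the responder analysis is labelled post hoc, with no between-arm test fixed, in a preliminary study of 50 patients.

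**Conclusion.** The point holds in conditional form. The plan makes every patient who stops early after improvement a responder without regard to the measured NRS, on an unblinded decision with no threshold. The combination arm has more contacts at which that decision can be made. The responder comparison can therefore favour that arm without a true effect.

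The direction assumes a similar chance per visit of being stopped in each arm; open-label expectation could add to it. An illustrative gap of about 7 points (q = 2%, 35% true response, stopping unrelated to response) is towards the unfavourable end for that q, and 1–2 points is the figure if most stoppers are real NRS responders.

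The mismatch with the continuous analyses is certain only for patients whose later values are missing, and it arises from the two rules together.

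A reader might go further and conclude that the trial's main efficacy result is compromised. It is not: the primary analysis is ODI change at week 4, and this rule does not enter it.

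**What to change.** Delete the automatic-responder rule in 2.8.4 and in 2.9, part D. Apply the 2.5-point NRS criterion to all patients in the efficacy set. For those who stopped early and have no later value, use the NRS scheduled at the early-termination visit in Table 1. This agrees with the economic section, which already carries the last measured value for patients who complete treatment early.

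State which NRS defines response, because back and leg pain are rated separately (2.8.2) and the responder definition says only NRS. Keep early termination as the separate outcome already planned. The automatic-responder version may be shown as a sensitivity analysis.

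The cost is a change of analysis wording. No new data are needed, and the conditions under which patients may stop are left as they are.

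There are two downsides. Some patients who stopped satisfied will no longer count as responders. The timing of the early-termination NRS will still be set by an unblinded decision, and the score is the patient's own, so the change reduces the dependence on open-label judgement but does not remove it.
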